### Recruitment and consent

*Phase 1:* All new patients at KCD and SBDC are first examined at the outpatient department (OPD). A brief history (including history of tobacco use) is taken by the dentist on duty, to reach a preliminary diagnosis, before referring the patient to the relevant department/ward for treatment. The first author will be present in the OPD and will brief the dentists working in the OPD about the study. Potential participants (patients) will be identified by the dentists, during history taking while working in the ‘OPD’ in the presence of the first author. Participants identified at the OPD will be invited by the first author to participate in the study. Senior dentist, from the five selected departments, will be invited face-to face by the first author to participate in this phase of the study. The study protocol will be discussed in detail and written informed consent will be sought, at least 24 h prior to the interviews.

*Phase 2 & 3:* The overall trial flow is outlined in Fig. 1. Potential participants for the pilot RCT, will be identified from the selected departments of the two dental hospitals. A pro-forma is filled for every new patient in the department, ‘which includes a detailed history of habits’ to reach a final diagnosis, before deciding the treatment plan for the patient. Potential participants will thus be identified by the participating dentists. Once the participants are identified, a member of the research team will discuss the study and invite them into the trial, before seeking written or thumbprint informed consent. All permanent faculty members and trainee medical officers, working in the selected wards will be invited, face-to-face by the first author, to participate in the trial for delivering the intervention. A copy of the signed informed consent form will be given to all trial participants(patients and dentists) for their records.

**Fig. 1 Fig1:**
[figure not shown]
Participants flow through the study.

### Intervention group

Participants in the intervention group will receive an adapted version of the structured behaviour support intervention for ST cessation, ‘BISCA’. While the intervention will be adapted upon completion of phase 1, a TIDieR checklist for the intervention prior to adaptation is provided (Table 1). BSICA has been developed by identifying key theory-based determinants, that govern early initiation and continued use of ST, in users of South-Asian origin. These determinants have been mapped to behaviour change techniques (BCTs) that are effective in behaviour change in general and in tobacco cessation in particular [24]. These BCTs have then been translated into the ‘intervention activities’ and further developed into a culturally appropriate resource to facilitate the delivery of these activities. It comprises 23 activities across three sessions. These include, providing information for raising awareness of ST harms and the benefits of quitting, boosting motivation and self-efficacy, and developing strategies to manage triggers, withdrawal symptoms, and relapse [16, 17]. BISCA will be delivered by dentists in three sessions namely; pre-quit, quit and post-quit sessions. All sessions will involve face to face counselling with the aid of a flipbook which contains interactive messages for the participants to view on one side facing the patient, whereas, the other side has prompts for the dentists to guide the conversation with the patients. The pre-quit session will be delivered on the participant’s first visit for their dental treatment. The aim of this session is to assess and develop the participants’ intention to change and to plan and prepare the participant for quitting. In this session, a ‘quit date’ will be set with the participant, which will be the date that the participant, agrees to quit tobacco. This date will coincide with the participants’ next dental visit. Participants will be given a take-home booklet (a copy of interactive cards) in this session, the purpose of which is to reinforce the messages delivered in the session. The ‘quit session’ will be delivered to the participants on their subsequent dental visit (2nd visit for their dental treatment). The aim of the quit session is to support the participant on the quit day. Focus in this session will be on withdrawal symptoms and managing triggers. Participants will be given a calendar for self-monitoring purpose in their 2^nd^ session, which they have to mark for the number of days that they have remained abstinent/or not. They will be asked to bring this calendar in their next visit. The third visit, ‘the post quit session’ will be scheduled alongside the third visit of the participant for treatment. The purpose of this session is to provide ongoing support and confirmation of abstinence. While we cannot be sure how long each session will last, based upon past experience of delivering BISCA in a community setting, the first sessions are expected to last for 4–54 min, the 2^nd^ session is expected to last 5–35 min and the last session is expected to last for 2–22 min.

**Table 1 Tab1:** TIDieR Checklist for the intervention-BISCA.

S. No.	Item	Definition
1	Brief name	Behavioural support Intervention for Smokeless Tobacco Cessation in South Asians (BISCA).
2	Why	Focused face-to-face behavioural support for tobacco cessation is very effective in increasing quit rates. Dentists are the first to notice any changes in the oral mucosa due to tobacco use. Most of the treatments require more than one visit. These factors place dentists in a unique opportunist position to identity tobacco users and offer quit advice and support for tobacco cessation. It is recommended that provision of quit advice and support by dentists should be integrated into their routine clinical practice.
3	What (materials)	*Participants (users):* Self-help calendars and take home booklet for the patients. The purpose of the take-home booklet is to reinforce the messages delivered in the sessions. Whereas, the calendar will be given for self – monitoring purpose ‘offered at the quit-session’. *Intervention providers (dentists*): Practice manual and interactive cards will be given to the participating dentists.
4	What (procedures)	Structured behaviour support ‘face-to-face counselling’ will be delivered by dentists in three sessions namely pre-quit, quit and post-quit sessions. *Pre-quit session*. The activities included in the pre-quit session are aimed to develop the users’ intention to change and to plan and prepare the user for quitting. *Quit session*. The activities included in this session are centred on a reflection on the preparation and support on the quit day. *Post quit session:* The purpose of this session is provision of ongoing support and confirmation of abstinence.
5	Who will Provide	Dentists trained in delivering BISCA.
6	How	BISCA will be delivered as an individual face to face conversation.
7	Where	Periodontology and Prosthodontics departments of KCD and SBDC.
8	When and How much.	BISCA will be delivered in three sessions. Each session will be delivered before or after the dental treatment is completed (as deemed appropriate by the dentist).Based upon past experience of BISCA in a community setting, the first sessions are expected to last for 4–54 min, the 2^nd^ session is expected to last 5–35 min and the last session is expected to last for 2–22 min. The sessions will scheduled one or two weeks apart.
9	Tailoring	The conversation will be tailored to the specific type of ST product used by the patient. Furthermore, the quit advice in the quit-session and continued support offered in the subsequent session will be guided by the level of patients’ motivation and engagement. The duration of the sessions will be dependent upon the interaction between the dentists and patient.
10	Modification	N/A
11	How well (planned)	Two ‘half-day’ workshop will be arranged to train all participating dentists to deliver BISCA. Training manual will be given to the dentists and they will be strongly advised to adhere to the manual for delivering the intervention. Fidelity to intervention delivery will be assessed via audiotaping the interactions between the dentists and patients.
12	How well (actual)	N/A

### Control group

The usual practice, in Pakistan, is no support for tobacco cessation. The participants in the control group will be given self-help material by the dentist, in the form of take-home booklet containing tobacco cessation messages (given in first visit). A TIDierR checklist is provided in Table 2.

**Table 2 Tab2:** TIDier Checklist-Self-help material.

No	Item	Definition
1	Brief name	Self-help material
2	Why	Self-material has some benefit of increasing quit rates in comparison to no intervention.
3	What (materials)	Take home booklet,(the same booklet given to intervention group).
4	What (procedures)	All patients will be offered the booklet in the 1^st^ visit.
5	Who provided	Dentists
6	How	The booklet will be handed over to the participants by the dentist during the 1^st^ visit.
7	Where	Periodontology and Prosthodontics departments of KCD and SBDC
8	When and How much	1^st^ visit(one booklet)
9	Tailoring	N/A
10	Modification	N/A
11	How well (planned)	N/A
12	How well (actual)	N/A

### Randomization procedure and concealment of allocation

Consented participants will be randomly assigned to the control (self-help material) or intervention arm, in a 1:1 ratio. An independent statistician will prepare a computer-generated randomisation schedule in random-sized permuted blocks. The allocation schedule will be contained in a sealed opaque envelope each bearing on the outside the name of the study site and a unique number for each participant. The sealed envelopes will only be accessible to the research team, only opening them after informed consent and baseline measures have been obtained.

### Blinding

Due to the nature of the intervention, the research team, participants and participating dentists will not be blinded to the assigned intervention.

### Pilot RCT visits and follow-up

Participants will be asked to attend three study visits, each approximately two weeks apart. These will be scheduled by the dentists treating the patient in line with the patient’s treatment. Additionally some of the participants will be asked to make an additional visit for interview ‘phase 3’.

### Withdrawal of study participants

Participants will be free to withdraw from the study at any point without giving a reason and without their legal rights or dental care being affected. However, the information collected will be retained and will be used confidentially for purposes relating to this research study only.

### Data collection and outcome measures

*Phase 1:* Demographic data will be collected from all participants in this phase. Qualitative data will be collected through semi structured, in-depth interviews, which will be audio recorded. The interview topic guide that will be used for interviews with the patients who are ST users, is guided by the Capability- Opportunity-Motivation-Behavior (COM-B) model [25]. The COM-B model recognizes behaviour as a product of an interrelated system which involves an individual’s or group’s capability (physical and psychological), opportunity (social and physical) and motivation (reflective and automatic) [25]. The guide will explore the patients’ ST behaviour (initiation, continued use, cessation attempts) and factors influencing those behaviours. Questions are organized according to the three domains of COM-B model i.e., knowledge of the associated health risks from ST use and skills in managing triggers (capability), access to cessation support via healthcare and the role of other people (opportunity), views and emotions about ST use and cessation (motivation) [17]. Additionally, their views about the contents of BISCA and trial will be assessed as well.

Likewise, dentists working in teaching hospitals have a wide and complex range of factors influencing their behaviour of offering cessation support to their patients in routine clinical practice. The topic guide that will be used for the interviews with the dentists will be guided by the COM-B model. The topic guide will thus enquire into dentist’s capability, the opportunities available to them and the factors influencing their motivation to offering behavioural cessation support in routine [15]. In addition to this, the guide will also include questions, to explore the current practices of the dentists and their views on the intervention (BISCA) and the trial processes. The first author will collect demographic data, conduct the interviews and audio record them.

*Phase 2 & 3*: Demographic information will be collected from all trial participants at baseline. ST use history will be collected using ST use questionnaire, which will be administered at baseline and in all subsequent visits. The Fagerstörm Tobacco and Nicotine Dependency scale for Smokeless Tobacco (FTND-ST) [26], Fagerstörm Test for Nicotine Dependence FTND and The Oklahoma Scale for Smokeless Tobacco Dependence (OSSTD) [27], will be used to measure nicotine dependence amongst participants. These scales will be administered at baseline and 3^rd^ visit.

The visits of the first 10% of the patients (control and intervention) will be audio recorded to, assess fidelity to the intervention and to ascertain cross-over between the two arms. Audio recordings, have an advantage over direct or in-person observation, in that direct observations can be potentially more intrusive and labour intensive and can influence the delivery/implementation [28]. Likewise, self-reports might be less labour intensive compared to audio recordings, however, there are concerns regarding the respondent misunderstanding the question or answering the questions quickly/carelessly [16, 28]. Fidelity, will be ascertained using the fidelity index for BISCA, which consists of 26-items. Of these, 22 items (representing the intervention components) are included in the ‘adherence index’ whereas, six items ‘assessing the competence with which the intervention is delivered’ are included in the ‘quality index’ [16]. The adherence of the participants to the intervention, will be assessed by estimating the completion rates of the calendars, that will be given to the patients at the quit-session.

All patients will be contacted telephonically, by the first author at three and six months after completion of their 3rd visit to assess their self-reported ST use.

Some of the trial participants ‘participating patients and dentists’ will be invited for interview, after intervention delivery, to get an insight into the views and opinions, regarding feasibility and acceptability of the intervention. Information about this will be given in the participant information sheet before recruitment of the trial. Whereas, separate informed consent will be sought by the first author from these participants prior to the interviews.

All personal data will be stored securely in order to protect confidentiality before, during and after the study. Minimal personal data will be collected and recorded on a demographic sheet against the participant IDs. All correspondence details will be deleted once no more needed. All the data will be de-identified using a participant ID. An encrypted audio recorder will be used for audio recording of the interactions between the dentists and the dental patients (participants) as well as interviews with the participants, before and after the trial.

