**Material and methods:**

The study will have 3 phases: (1) Adapt a previously developed intervention to make it suitable for delivery in a clinical/dental setting through qualitative interviews with dental patients and dentists; (2) A multi-centre, pilot randomised control trial in two teaching dental hospitals in Pakistan. Participants (dental patients) will be randomly assigned to intervention or control group in a 1:1 allocation ratio to receive either a structured behavioural support intervention involving face to face counselling or self-help material plus usual care. Each participant will be in the study for approximately 6 months and the overall study is expected to run for 12 months; (3) An embedded qualitative process evaluation. All trial participants will be followed up at 3 and 6 months to assess self-reported ST use. Outcome measures will include: rates of eligibility, recruitment and retention, randomisation group cross-over rates, the provision of data on ST use behaviour, fidelity to the intervention and qualitative assessment of acceptability and feasibility.

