### Study sites

This study will be carried out in Peshawar, which is the capital city of Khyber Pakhtunkhwa (KP), the north-western province of Pakistan, where the use of Naswar is most common. The study will be conducted at two specialised tertiary level, dental teaching hospitals in Peshawar: a public sector facility, the Khyber College of Dentistry (KCD); and a private sector facility, the Sardar Begum Dental College (SBDC). Being the only public sector specialized dental hospital in Peshawar, KCD caters to most of the urban and rural population of Peshawar as well as nearby areas.ST use has been linked to low socioeconomic status and since services are offered at nominal rate at KCD, it is believed that most of the patients visiting this hospital belong to low socioeconomic class. It is hoped, that the choice of this site will make patient recruitment easier. In order to explore how intervention delivery varies across public and private hospitals, SBDC has been selected as the 2nd study site. Both the study sites have expressed their support for the study in writing by issuing ‘letter of support’ signed by the deans of the hospitals.

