
*Phase 2 and 3:* The trial participants will be recruited from the periodontology and prosthodontics departments of the selected hospitals. The choice of recruitment of dental patients from periodontology and prosthodontics is based on practical as well as biological grounds. ST use, is a potential risk factor for periodontal changes, such as gingival recession [18], attachment loss [19, 20], which can contribute towards tooth loss. Therefore, it is believed that a substantial number of patients using ST, will be visiting these departments. Furthermore, in most cases, patients referred to these departments require multiple visits for the completion of their treatment. However, if we are unable to recruit the required sample size within the stipulated time, then recruitment will be done from the department of ‘operative dentistry/endodontics’ as well.

Participants will be dental patients visiting SBDC/KCD, for a dental treatment and who are 18 years and above, are regular ST users, are willing to visit the study site for three visits and willing and able to provide written or thumbprint informed consent. Patients who are currently accessing cessation support or/and are unable/unwilling to provide written or thumbprint informed consent will be excluded. The intervention will be delivered by consenting, licensed dentists, working as faculty members or post-graduate trainees, at the selected wards/department of KCD and SBDC. These dentists will be trained in intervention delivery prior to the recruitment of patients.

In line with good practice recommendations, no formal sample size calculation has been completed for this pilot study [21]. Recommendations suggest, sample sizes of 30 or more participants in each arm [22, 23]. We anticipate an attrition rate of 36% from a similar feasibility trial [16] and hence, aim to recruit 50 participants in each arm.

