An embedded qualitative process evaluation (phase 3) will be undertaken for which some of the trial participants and participating dentists will be invited, for face-to-face interviews, after completion of all trial visits. The purpose of these interviews is to qualitatively assess, the acceptability and feasibility of the intervention. A non-probability sampling approach will be used and at this stage it is anticipated that 10–12 patients who participated in the trial will be interviewed. Taking 5, 6 patients from each study site and at least 1 patient from each of the 15 year age bracket, from 18–78 years; as stated above in phase 1. As for the dentists, we anticipate interviewing 10–12 dentists who participated in the trial. It is anticipated that at least, 2–3 dentists will participate from each department, since we propose to conduct the trial in two departments at each study site, providing approximately 8–12 dentists in total. We aim to interview all dentists who participated in the intervention delivery. Equal number of respondents will be selected from each of the two study sites.

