### Outcomes

Outcome measures will include: rates of eligibility, recruitment and retention, the provision of data on; ST use behaviour, self-reported ST use, FTND-ST, OSSTD and self-reported quit rates, fidelity to the intervention and qualitative assessment of acceptability and feasibility.

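### Audio recording only the first 10% of patients ties fidelity and cross-over to the earliest visits, so later drift or accumulating contamination cannot be seen; spread the same recordings over recruitment

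*Protocol article*

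**What the plan says.** The protocol article, under Data collection and outcome measures (Phase 2 & 3), fixes the recorded sample: "The visits of the first 10% of the patients (control and intervention) will be audio recorded to, assess fidelity to the intervention". The sentence then gives the recordings a second purpose: "and to ascertain cross-over between the two arms". Two measures therefore rest on one set of recordings. Table 1 names audiotaping as the way fidelity is assessed and adds no other method. The Data collection section gives reasons for preferring audio to direct observation and to self-report.

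The sample size is under Participants and sampling: "We anticipate an attrition rate of 36% from a similar feasibility trial [16] and hence, aim to recruit 50 participants in each arm". The phase 3 paragraphs there expect two to three dentists per department in two departments at each site, "providing approximately 8–12 dentists in total". Study sites gives the reason for the private hospital: "In order to explore how intervention delivery varies across public and private hospitals, SBDC has been selected as the 2nd study site".

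The abstract lists "randomisation group cross-over rates" among the outcome measures. The Outcomes section starts "Outcome measures will include: rates of eligibility, recruitment and retention, the provision of data on; ST use behaviour" and goes on to name fidelity, but nowhere in its list mentions cross-over. The Analysis section reports feasibility rates with 95% confidence intervals and the fidelity index as mean and SD.

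**The concern.** Patients are randomised individually. Dentists are trained in the intervention before the first patient is recruited and know each patient's allocation. Dentists deliver the counselling in one arm and hand out the booklet in the other. The article assigns no separate dentists to the two arms, so the same dentists can be expected to treat both.

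In such a design, two things may change over time: how fully the sessions are delivered as training recedes, and how much of the counselling reaches controls as dentists grow used to it. A sample taken only from the first patients says nothing about either. It also leaves to chance whether both hospitals are usefully represented, although comparing delivery between them is the stated reason for having two.

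At stake is what the pilot can hand to the definitive trial it is meant to prepare. Cross-over bears on whether patients can again be randomised individually within a dentist's practice, and fidelity bears on how much supervision is needed. Visits that were not recorded cannot be recovered afterwards.

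**Working it through.** **1. The plan's own figure.** The inputs are the advice of "sample sizes of 30 or more participants in each arm" and 36% attrition. Inflating gives 30 / (1 − 0.36) = 46.9, so 47 per arm. The plan takes 50, which leaves 50 × 0.64 = 32 completers, still above 30. The target of 50 is a rounded-up figure and is not in question.

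**2. Size of the recorded sample.** 10% × 100 = 10 patients, about 5 per arm at 1:1. Block sizes are not given. Assuming blocks of 2, 4 and 6 and five recorded patients per site, simulation puts the intervention count at 4 to 6 in about 99% of runs. Ten patients at three visits make 30 recordings, about 15 of them intervention sessions. If the 36% attrition fell before visit 3 (an assumption), 5 × 0.64 = 3.2, so about 3 of the 5 intervention patients would be recorded through the whole course.

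**3. Precision of cross-over.** With no events among n, the exact 95% upper limit is 1 − 0.025^(1/n).
- n = 5 (controls): 1 − 0.025^(1/5) = 52%.
- n = 10 (both arms pooled): about 31%.
- One event in 5: exact interval 0.5% to 72%.

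The chance of seeing no cross-over in 5 controls is (1 − p)^5. The values of p are illustrative, since the article gives none.

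| True rate p | Chance of 0 in 5 |
|---|---|
| 5% | 77% |
| 10% | 59% |
| 20% | 33% |

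**4. Precision of fidelity.** The 95% half-width of a mean is t(0.975, n − 1) × SD / √n. For n = 5 this is 2.776 / 2.236 = 1.24 SD.

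**5. Coverage of dentists and sites.** If each patient stays with one dentist (an assumption), 5 intervention patients reach at most 5 dentists: 5/8 = 62% down to 5/12 = 42%. If patients fall to dentists at random, about 4 are reached. Split evenly, each site would supply 2 or 3 recorded intervention patients. The article does not say whether the first 10% is counted overall or by site.

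**6. Coverage of time.** None of the remaining 90 patients is recorded. With no later observation, change over time cannot be estimated, whatever the first ten show. Steps 3 and 4 describe small numbers, which any sample of ten shares; this step describes the selection rule itself.

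**7. Other sources in the article.** Calendar completion measures patients' adherence. The phase 3 interviews cover acceptability and feasibility of the intervention and trial procedures. Neither yields a fidelity score or a cross-over rate.

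**The case against.** The strongest reply is that this is a pilot with no formal sample size calculation and a descriptive analysis, so wide intervals are expected. That stands: the 52% limit alone would not justify a change. The plan also aims to interview every delivering dentist after the trial visits, so later delivery is not wholly unexamined, although interviews cannot supply a rate. Early recordings may also be useful for prompt feedback to dentists, though the article claims no such purpose.

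Stronger readings are tempting, and the documents do not support them:
- A reader might infer that contamination cannot occur in the first patients, so that the rule drives the estimate toward zero. Dentists are trained before recruitment, so a control patient could be counselled from the first day. Early delivery might even be the least disciplined. A downward bias is plausible but not shown.
- A reader might infer that a fixed share of dentists will certainly go unrecorded. The percentages in step 5 hold only if one dentist sees a patient throughout; the article says merely that visits are scheduled by the treating dentists.
- A reader might infer that the private site will be under-represented. The article gives no recruitment split, and an unstratified random sample of ten would carry the same risk. What can be said is that balance is not guaranteed.
- A reader might infer that the next trial's unit of randomisation will be chosen wrongly. No progression rule in the article ties cross-over to that choice; the link is a reasonable inference about how the result would be used.

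The absence of cross-over from the Outcomes section is a reporting inconsistency. It does not itself bear on how patients are sampled.

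**Conclusion.** The point holds as a worthwhile, inexpensive improvement, not as a flaw that invalidates the pilot. The only stated source for two declared measures is the earliest tenth of patients, about 5 per arm. That sample cannot reveal later loss of fidelity or contamination that grows with practice, and it secures neither both sites nor most dentists. A near-zero cross-over result would be weak reassurance: the upper limit is 52% for 0 of 5, and such a result would occur 59% of the time if the true rate were 10%.

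The conclusion rests on 100 patients being recruited, on roughly equal arms among those recorded, and on dentists serving both arms, which the article implies without stating it outright. It does not rest on any assumed trend in contamination. Whatever the trend is, the present rule cannot show it.

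**What to change.** Replace the first 10% with about 10 patients chosen at random across the whole recruitment period. Balance them by arm, site and early or late period, which gives 2 × 2 × 2 = 8 cells and fits within 10 patients. Spread them over as many dentists as possible. Do not stratify fully by dentist: arm, dentist and three periods would need 8 × 2 × 3 = 48 to 12 × 2 × 3 = 72 cells, against 30 recordings. Record all three visits of each selected patient, because the intervention's activities run across three sessions and isolated visits would not give a score for the whole course.

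The statistician who prepares the allocation schedule could mark the selected patients inside the sealed envelopes, so that the mark does not reveal allocation before consent and baseline.

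Add the cross-over rate to the Outcomes section, matching the abstract, and report it with its 95% interval.

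Optionally, ask every control patient one question on whether the dentist counselled them with the flipbook. With all 50 answering and no positives, the upper limit is 1 − 0.025^(1/50) = 7.1%; with 32 answering it is 1 − 0.025^(1/32) = 10.9%. Given the article's own reservations about self-report, this should supplement the audio and not replace it.

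Cost: the number of recordings is unchanged. The recorder must be available at both sites throughout, consent to recording must be sought from all participants, and any use of the first recordings for early feedback is reduced. The optional question adds one item.

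### The 3- and 6-month calls are timed from completion of visit 3, so a participant who does not complete that visit has no call date

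*Protocol article*

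**What the plan says.** The protocol article, Data collection and outcome measures (Phase 2 & 3), sets the calls: "All patients will be contacted telephonically, by the first author at three and six months after completion of their 3rd visit". The Abstract (Material and methods) promises the same coverage without a starting point: "All trial participants will be followed up at 3 and 6 months to assess self-reported ST use". It also says: "Each participant will be in the study for approximately 6 months".

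The visits are described under Pilot RCT visits and follow-up, for participants in general: "Participants will be asked to attend three study visits, each approximately two weeks apart". On who sets the dates, the same section says: "These will be scheduled by the dentists treating the patient". The Blinding section states that these dentists know the allocation. Table 1, item 8 (Intervention group), spaces the counselling differently: "The sessions will scheduled one or two weeks apart".

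In the intervention arm, "a ‘quit date’ will be set with the participant" at the first session, to fall on the second dental visit. The third visit is the post-quit session. The control arm receives one booklet at the first visit (Control group, Table 2). The tobacco-use questionnaire at every visit and the dependence scales at visit 3 are described without separating the arms.

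On losses, Participants and sampling says: "We anticipate an attrition rate of 36% from a similar feasibility trial".

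**The concern.** The follow-up clock starts at an event that occurs after randomisation and requires attendance. The rule promises a call to everyone, but can be applied only to those who complete visit 3. Someone who drops out of dental treatment after the first visit is still a trial participant, yet has no date from which to count.

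The Outcomes section names retention, provision of tobacco-use data and self-reported quit rates. The Analysis section reports feasibility rates with 95% confidence intervals and compares quit rates between groups. If staff apply the rule as printed, these figures describe people who kept attending, and attendance is likely to go with motivation to quit. The Discussion presents the study as groundwork for a definitive trial, so a retention rate obtained this way could mislead its planning.

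A second, smaller effect is that time from randomisation to each call depends on how quickly the dental visits happen.

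**Working it through.** **Inputs.** From Participants and sampling: 50 recruits per arm, 36% attrition and a guideline of 30 or more per arm. From Table 1, item 8: gaps of 1 or 2 weeks. From Pilot RCT visits and follow-up: gaps of about 2 weeks. Assumptions: randomisation falls on the day of visit 1 (envelopes are opened after consent and baseline measures, and the booklet or pre-quit session is given at the first visit); 3 months = 13.0 weeks; 6 months = 26.1 weeks; 1 month = 4.345 weeks; attrition is equal in the two arms.

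**The plan's own figure.** 30 / (1 − 0.36) = 46.9, so 47 per arm. The plan recruits 50, which leaves 50 × 0.64 = 32 per arm. Fifty is a rounded-up figure that meets the guideline, and nothing here turns on it.

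**Participants without a call date.** Expected losses are 0.36 × 50 = 18 per arm. The number without a date is 18 × (share of losses before visit 3), and the article does not give that share.

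| Share of losses before visit 3 | No call date, per arm | No call date, of 100 |
|---|---|---|
| None | 0 | 0 |
| Half | 9 | 18 |
| All | 18 | 36 |

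**What this could do to retention.** This is an illustration, with 32 of 50 per arm finally reached. Over the number randomised, retention is 32/50 = 64% in every row. Over those with a call date, it is 32/50 = 64%, 32/41 = 78% or 32/32 = 100%. The article does not say that the second denominator will be used, but the call rule invites it.

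**Timing since randomisation.** Visit 3 falls at 2 × gap. The calls fall at 13.0 + 2 × gap and 26.1 + 2 × gap weeks.

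| Gap | Visit 3 | 3-month call | 6-month call | Time in study |
|---|---|---|---|---|
| 1 week | week 2 | week 15.0 | week 28.1 | 6 + 2/4.345 = 6.5 months |
| 2 weeks | week 4 | week 17.0 | week 30.1 | 6 + 4/4.345 = 6.9 months |
| 3 weeks (assumed slippage) | week 6 | week 19.0 | week 32.1 | 7.4 months |
| 4 weeks (assumed slippage) | week 8 | week 21.0 | week 34.1 | 7.8 months |

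Within the stated gaps the spread is 30.1 − 28.1 = 2 weeks. If both arms keep the two-week schedule, the planned difference between arms is 30.1 − 30.1 = 0 weeks. A systematic 2-week difference would need, for example, one arm at 1-week gaps and the other at 2-week gaps, which the article does not plan.

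**The case against.** The strongest reply is that the text commits to calling everyone and nowhere restricts the calls, or any denominator, to visit-3 completers. On that view a missing fallback date is detail for the full protocol, and a descriptive pilot can tolerate it. Part of this stands. The article excludes nobody, and the full protocol may contain a fallback rule. But the starting point is printed explicitly and is the only one given. It cannot be applied to everyone it names, so this is a stated rule that works badly and not merely an omission.

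Several stronger readings are tempting, and the documents do not support them:

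- A reader might infer that the two arms are measured at different times. The visit schedule is one schedule for all participants, and eligibility requires everyone to be willing to make three visits. A difference could arise in practice, because unblinded dentists set the dates and only the intervention arm has counselling at visits 2 and 3. It is a possibility, not part of the plan.
- A reader might infer that visits 2 and 3 are empty for controls. They carry no counselling there, but the questionnaires are described for all trial participants.
- A reader might take 18 per arm as the expected number without a date. It is the top of a range that starts at 0.
- A reader might treat 6.5 to 6.9 months as a serious conflict with the Abstract. The Abstract gives an approximate figure, so the discrepancy is small. The spacing statements also overlap, and Table 1 describes the intervention before adaptation.

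Counting from visit 3 also has a rationale in the intervention arm, since it fixes the interval after the last session. It has no such meaning for controls, whose intervention ends with the booklet at visit 1.

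**Conclusion.** The point holds for the missing call date. The only stated starting point depends on attendance after randomisation, and it conflicts with the commitment to follow everyone. It affects 0 to 18 of 50 participants per arm, depending on an unstated share of the 36% attrition. If the rule is followed literally, follow-up data, retention and quit rates become conditional on attendance.

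The timing effect is minor: about 2 weeks of variation on calls that fall at weeks 28 to 30, with no planned difference between arms and only a possible one in practice. These figures assume randomisation at visit 1 and equal attrition in the arms. With descriptive analysis only and no formal sample size calculation, this is a worthwhile correction and not a flaw that invalidates the pilot.

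**What to change.** Time both calls from the date of randomisation for every randomised participant in both arms, whether or not visits 2 and 3 were attended. Define retention in each arm as the number with a completed call divided by the number randomised. All 100 participants then have a due date, the calls fall at about weeks 13 and 26, and time in study matches the Abstract.

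The number of calls and the sample size do not change. There are two costs. The calls come about 2 to 4 weeks sooner after the last session and after the quit date than now planned. For the last session, the interval before the 6-month call becomes 26.1 − 4 = 22.1 to 26.1 − 2 = 24.1 weeks, instead of 26.1. Anyone already in follow-up also needs a transition rule. The article reports that data collection began on 23 October 2021, without saying whether trial follow-up had started.

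Separately, reconcile the visit spacing in Table 1 with that under Pilot RCT visits and follow-up, and the time in study in the Abstract with the call rule.
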